#### Participant timeline {13}

In the first year of this five-year study, we will recruit mother-child dyads from Poriborton close to the birth to ensure the continuation of LPG supply in the intervention arm. We commenced recruitment in 2021, and it will take up to 3 years for the whole cohort of children to reach 24 months of age to complete follow-up. Data cleaning and preliminary analysis will be substantial and will require a year. Field activities will wind down in year 4. Final analyses and manuscript preparation will be moved to Sydney in year 5.

#### Sample size {14}

We expect the final sample size to be at least 1854 children (927 in each arm) with follow-up up to 24 months of child’s age available for analysis. This assumes ten per cent loss-to-follow-up due to mortality in the first 2 years of age (3%), migration out (3%), and withdrawals (2%). For this sample size, we have at least 88% power to detect a 20% lower risk (relative risk =0.8) in stunting, assuming 35% stunting in the control vs 28% in the intervention, an intraclass cluster correlation of 0.02, which is based on the previous cRCT on stunting, [26] and a two-sided significance level of 0.05. If the intraclass correlation is twice as large, i.e., intraclass correlation 0.04, [25], we would still have 80% power. For the secondary outcomes, the final sample size will provide at least 80% power to detect moderate effect sizes for many, if not all, secondary outcomes. For example, we will have 90% power to detect a standardized difference of 0.2 between arms for height-for-age *z*-score. Any differences in perinatal outcomes from Poriborton will not impact the integrity of the extension. We expect reduced perinatal mortality and higher birth weights. Additional live births will result in a slightly higher sample size in the intervention arm for the extension. We investigated this scenario in our power calculation and found the differences in cluster size will remain relatively small and less likely to impact the power.

For the personal exposure of household air pollution, a sample size of 120 children from each arm will be used to estimate reductions in PM2.5. This sample size will allow us to detect a 28% difference (50% and 70% in intervention and control, respectively) (WHO target [3]) with > 80% power.

The expected number of live births (> 7 days old) eligible is 2154, corresponding to all women enrolled in Poriborton from October 2020, of which we expect 10% fetal loss and up to 5% lost-to-follow-up due to migration (3%) or withdrawal (2%). Of the 2154 births (infants), we expect 2060 to be enrolled into the Poriborton-Extension, conservatively assuming that 4% of the newborns die prior to enrollment or decline to participate in the extension.

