### Assignment of interventions: allocation

#### Sequence generation {16a}

We will use the existing clusters and randomization allocation from the Poriborton trial. These clusters were computer generated using random sequences. In Poriborton, we selected 206 clusters from 16 selected unions of 2 sub districts. The clusters were then randomized with a ratio of 1:1 into LPG and control arm, with 103 clusters in each arm.

The ratio of clusters per arm in each block will be 1:1 for intervention vs. control arm. For Poriborton, we generated random blocks of sequential 1 and 2 using Stata SE, where each number represented either the intervention or control arm. Non-investigators then allocated the clusters to the treatment arms based on the random sequence.

For the Poriborton Extension Trial, we will continue with the same mother-child dyads from the original randomization of the Poriborton trial for this extension of the trial (Fig. 2).

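### The stated minimum of 88% power for stunting is about 85% for the 1854 children to be analysed, and the itemised losses sum to 8%, not ten per cent

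*Protocol article*

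**What the plan says.** The Sample size section of the protocol article sets the analysed number first: "We expect the final sample size to be at least 1854 children (927 in each arm"). The power statement refers to that number: "For this sample size, we have at least 88% power to detect a 20% lower risk (relative risk =0.8) in stunting". The inputs are given alongside it: "assuming 35% stunting in the control vs 28% in the intervention", "an intraclass cluster correlation of 0.02" and "a two-sided significance level of 0.05". The section adds that power would still be 80% if the intraclass correlation were 0.04.

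The number of clusters is in the Sequence generation section, which carries the parent trial's clusters and allocation into the extension, "with 103 clusters in each arm".

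The loss allowance reads: "This assumes ten per cent loss-to-follow-up due to mortality in the first 2 years of age (3%), migration out (3%), and withdrawals (2"%). The section expects 2060 children to be enrolled.

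For a secondary outcome, height-for-age z-score, the section says: "we will have 90% power to detect a standardized difference of 0.2 between arms". It gives no intraclass correlation for that outcome.

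**The concern.** Every input needed to recompute the primary-outcome power is in the document, and the recomputed value falls short of a figure presented as a minimum. The error is in the favourable direction. On the protocol's own assumptions the type II error is about 14.5%, not 12%, and a reader weighing a null result on stunting would start from the wrong figure. Two further figures in the same section invite a check: the loss components, which do not add up to the stated total, and the height-for-age power, which looks low beside the stunting intraclass correlations.

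**Working it through.** **Inputs.** From Sample size: 927 per arm analysed, 35% versus 28%, intraclass correlation (ICC) 0.02 or 0.04, two-sided 0.05, 2060 enrolled (1030 per arm). From Sequence generation: 103 clusters per arm.

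**Formulas.** With n children per arm and m = n/103 per cluster, the design effect is DE = 1 + (m − 1) × ICC and the effective size is n/DE. With unpooled variance, SE = √[(0.35 × 0.65 + 0.28 × 0.72)/(n/DE)] = √[0.4291/(n/DE)] and power = Φ(0.07/SE − 1.96). The pooled version uses 0.315 × 0.685 × 2 = 0.43155 for the null variance.

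**Step 1: the stated 80% at ICC 0.04 is reproduced.** m = 927/103 = 9; DE = 1 + 8 × 0.04 = 1.32; effective size 927/1.32 = 702.3. Power is 80.8% unpooled and 80.7% pooled. This supports both the method and the cluster count.

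**Step 2: the stated 88% at ICC 0.02 is not.** DE = 1 + 8 × 0.02 = 1.16; effective size 927/1.16 = 799.1; SE = √(0.4291/799.1) = 0.02317; 0.07/0.02317 = 3.02; Φ(3.02 − 1.96) = 85.6%. The pooled version gives 85.4%.

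**Step 3: the choice of method does not explain the gap.** Other two-sided, equal-cluster calculations at 927 per arm and ICC 0.02:

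| Variant | Power |
|---|---|
| Continuity-corrected | 84.2% |
| log relative risk | 85.0% |
| t with 204 df | 85.2% |
| log odds ratio | 85.3% |
| arcsine | 85.5% |
| Hayes–Bennett | 85.3% to 85.7% |

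One-sided 0.05 gives 91.5%, so it does not explain 88% either. Unequal clusters lower the pooled figure, with DE = 1 + [(CV² + 1)m − 1] × ICC, to 85.0% at a cluster-size CV of 0.3 and 84.1% at 0.5. These CVs are assumptions; the document gives none.

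**Step 4: what would give 88%.** With 103 clusters per arm and ICC 0.02, about 1018 analysed per arm are needed. With 927 per arm, the ICC would have to be about 0.009.

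| Per arm | Clusters per arm | Power, ICC 0.02 | Power, ICC 0.04 |
|---|---|---|---|
| 927 | 103 | 85.4% | 80.7% |
| 1030 | 103 | 88.3% | 83.5% |
| 927 | 206 | 88.1% | 86.0% |
| Stated | | at least 88% | 80% |

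No row matches both stated powers.

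**Step 5: loss to follow-up.** 3% + 3% + 2% = 8%. The analysed number comes from ten per cent: 2060 × 0.90 = 1854. With 8%, 2060 × 0.92 = 1895, about 948 per arm, and power at ICC 0.02 is 86.1%, still below 88%.

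**Step 6: height-for-age, conditional.** If the stunting ICCs also applied here, power for 0.2 SD would be Φ(0.2/√(2/799.1) − 1.96) = 97.9% at 0.02 and Φ(0.2/√(2/702.3) − 1.96) = 96.3% at 0.04. The stated 90% needs an effective size of (1.96 + 1.2816)² × 2/0.2² = 525 per arm, so DE = 927/525 = 1.77 and ICC ≈ 0.77/8, about 0.095.

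**The case against.** The strongest reply is that little depends on this. The gap is about 2.5 points, base-case power is above 80%, the Recruitment section relies on the count of 1854 and not on the power figure, and the Trial status section reports recruitment completed in February 2022. All of that stands and limits the weight of the point. It does not make the figure right.

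Three stronger readings are tempting, and the document does not support them.

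- A reader might infer that the authors computed power on the 2060 enrolled and forgot the loss. The 88% fits that, but the 80% at ICC 0.04 fits 1854 (80.7%) and not 2060 (83.5%). The source is unknown, and the shortfall at 1854 does not depend on it.
- A reader might infer that the 80% figure at ICC 0.04 also fails. With equal clusters it is correct. It falls below 80% only with an assumed cluster-size CV of about 0.3 or more (79.7% at 0.3, 78.1% at 0.5, pooled formula).
- A reader might infer that the 90% for height-for-age is wrong. The protocol ties 0.02 and 0.04 to stunting only, and a larger ICC for height-for-age would produce 90%. If there is an error, it understates power, and the figure is given only as an example for a secondary outcome.

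The loss mismatch is likewise conservative: the itemised 8% would leave more children than 1854.

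**Conclusion.** The point holds for the primary outcome. On the protocol's own inputs, 1854 analysed children give about 85% power at ICC 0.02, not at least 88%. This rests on 103 clusters per arm all contributing about 9 children each; variation in cluster size would lower it slightly. The stated 80% at ICC 0.04 is consistent with 1854, so the two stunting powers appear to rest on different inputs. The loss components are 2 points short of the rate that produces 1854.

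The height-for-age figure is a secondary query. It would be about 96% to 98% if ICCs of 0.02 to 0.04 applied, but the document does not say that they do. Nothing here shows an inadequate sample size.

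**What to change.** In the Sample size section:

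1. Restate the primary power as about 85% for 1854 children analysed (103 clusters per arm, 9 per cluster) at ICC 0.02, and about 80% at ICC 0.04, assuming roughly equal cluster sizes. If 88% was meant for the 2060 enrolled before loss, say so and give the figure for 1854 beside it.
2. Make the loss components sum to the rate used, either by naming the missing 2% or by using 8% and updating the analysed number and its power.
3. State the ICC behind the 90% for height-for-age, or update that figure.

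The cost is a text correction and a slightly less favourable stated power. Enrolment, design and analysis are unchanged.

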#### Recruitment {15}

The Poriborton Extension Trial will enroll mother-child dyads from the original Poriborton trial. This extension phase will require a sample size of 1854 which is a subset of the original trial. We will enroll women who give birth to a liveborn infant who survives to or from 15 June 2021, and this will give us the required sample size for this extension trial.

### Assignment of interventions: allocation

#### Sequence generation {16a}

We will use the existing clusters and randomization allocation from the Poriborton trial. These clusters were computer generated using random sequences. In Poriborton, we selected 206 clusters from 16 selected unions of 2 sub districts. The clusters were then randomized with a ratio of 1:1 into LPG and control arm, with 103 clusters in each arm.

The ratio of clusters per arm in each block will be 1:1 for intervention vs. control arm. For Poriborton, we generated random blocks of sequential 1 and 2 using Stata SE, where each number represented either the intervention or control arm. Non-investigators then allocated the clusters to the treatment arms based on the random sequence.

For the Poriborton Extension Trial, we will continue with the same mother-child dyads from the original randomization of the Poriborton trial for this extension of the trial (Fig. 2).

#### Concealment mechanism {16b}

This is a cluster design and concealment, and blinding is impracticable. Field evaluation staff will be blinded to the hypothesis, and we will conduct our analysis blinded to the treatment arms.

#### Implementation {16c}

An independent statistician will generate the allocation sequence. All participants in the intervention clusters will continue receiving the intervention from the original Poriborton trial, and all participants in the control arm continue their usual cooking practice and do not receive any intervention. To minimize bias, since participant blinding is not possible, we have separate intervention and evaluation staff. Trial evaluators will be blinded to the hypothesis, and we will conduct our analysis blinded to the treatment arms.

### Assignment of interventions: blinding

#### Who will be blinded {17a}

This is a cluster design and concealment, and blinding is impracticable. Field evaluation staff will be blinded to the hypothesis, and we will conduct our analysis blinded to the treatment arms. Separate field staff teams are in operation for the intervention implementation and assessment measurement, which prevents measurement bias.

#### Procedure for unblinding if needed {17b}

The design is open label with only outcome assessors being blinded so unblinding will not occur. Blinding is not possible for the intervention and outcome assessment teams as we are giving a stove and LPG cylinders to the intervention participants, however the outcome assessors and data collectors will not be informed of the outcome for the Poriborton extension phase.

### Data collection and management

#### Plans for assessment and collection of outcomes {18a}

Separate field staff teams are in operation for the intervention implementation and assessment measurement, which prevents measurement bias.

##### Child anthropometry

Trained research assistants will collect anthropometric data (weight and height measurements) using in-field electronic data capture on tablets and established methods [27], which will be standardized before and during data collection. Anthropometry will be collected at 6, 12, 18, and 24 months of child’s age. We will use the WHO Growth Standard [28] to construct anthropometric indices and standard indicators, including stunting (height-for-age < − 2 Z), wasting (weight-for-height < − 2 Z), and underweight (weight-for-age < − 2 Z). Children with very low weight-for-height (Z < − 3) will be referred for assessment and treatment for severe acute malnutrition and retained in the study.

##### Bayley Scales of Infant and Toddler Development (IV) and Wolke’s behavior rating

Appropriately qualified and trained staff will conduct the Bayley tests as per the manual. The three key developmental domains include cognition, language, and motor will be assessed with the Bayley Scale. In addition, we will directly rate children’s five behaviors (approach, activity, emotional tone, cooperativeness, and vocalization) using the 9-point scale of the Wolke’s behavior rating during the Bayley test. Our team has expertise in using these tools in community trials in Bangladesh, and until now, several versions of Bayley have been translated, adapted, and used in Bangladesh [29, 30]. This time we will use Bayley - IV, which is the most updated edition and more culturally appropriate. We will collect data at age 12 and 24 months.

##### Infant and young child feeding practices

Infant and young child feeding (IYCF) practices are an important determinant of child growth and development. We will collect IYCF information by a 24-h recall questionnaire used in the national survey and several previous longitudinal studies trials [31, 32]. IYCF data will be collected at 3, 6, 12, 18, and 24 months of child’s age.

##### Family care indicator

To evaluate the amount of stimulation the child receives at home, we will use the family care indicator developed by UNICEF and initially validated in Bangladesh by our team. These questions will be asked to mothers/caregivers at the time of the Bayley test and will pick up information about child and caregiver interactions as well as availability of stimulation/play materials at home [33].

##### Food security

Food security will be assessed at 3, 12, and 24 months using the locally adapted household food security assessment tool [34]. We used a locally adapted standard Household Food Insecurity Access Scale tool [35]. We are currently implementing this into our data collection for the original trial.

##### Respiratory symptoms

The difference in respiratory symptoms in children and their elder siblings (spill-over effect, in children aged > 2) between the two arms is defined as the number of annual cough episodes lasting ≥ 4 weeks [36] and collected at 6, 12, 18, and 24 months using a validated questionnaire [37].

##### HAP exposure

We will measure personal HAP exposure in two ways: using our (1) structured questionnaires used in Poriborton [38], which include smoking in the home, and other known household air pollution variables, and (2) particulate matter: continuous by nephelometry and time-averaged filter-based measurements of particulate matter PM2.5 concentrations. Also, time-averaged black carbon, brown carbon, and tobacco smoke mass concentrations from the filter [39]. The Enhanced Children’s MicroPEM (ECM) is designed specifically for children aged less than 5 years. For children who are not mobile and are carried by their mother, the ECM will be carried by mothers. Once the children are mobile, the device will be worn by the child. [name] and his team have used this successfully and safely in South Africa and Malawi. It weighs ~ 150 g and is worn in a culturally appropriate pouch (that we developed) and collected at 6, 12–16 months, and 24 months of age.

##### Gender roles

The impact on gender roles is an essential consideration in understanding the impact of Poriborton-Extension. Women are usually responsible for household cooking, and women are disproportionately exposed to fumes from biomass stoves due to these responsibilities [40]. We will evaluate the impact of the intervention to changes in gender roles, i.e., shifts in the division in of labor, self-efficacy, woman’s access to and control over resources, altered work and time usage (due to less time collecting biomass fuels), household decision-making or bargaining power, and domestic violence. We will use specifically tailored tools, including relevant components from the Project-Level Women’s Empowerment in Agriculture Index [41] and an adapted version of the Clean Cooking Alliance’s “Follow-up In-person User Social Impact Survey” [42]. We will collect data at the 6 months and 18 months points of the intervention.

The timeline for scheduled visits and assessments for the Poriborton Extension Trial is found in Table 1.

**Table 1 Tab1:** Schedule visit and assessments of the Poriborton Extension Trial

	Tool	Birth	7–10 day	3 months	6 months	12 months	18 months	24 months
**Anthropometry**								
Length	Anthro	Y	Y	Y	Y	Y	Y	Y
Weight	Anthro	Y	Y	Y	Y	Y	Y	Y
MUAC	Anthro					Y	Y	Y
Head circumference	Anthro	Y	Y	Y	Y	Y	Y	Y
**Development**								
Bayley scores	Bayley’s Scales (IV) of Infant &Toddler Development and Wolke’s behavior rating					Y		Y
Family care indicator	UNICEF’s Family Care Indicator tool					Y		Y
**Child feeding**								
Initiation of Breastfeeding	Post-birth	Y	Y (if not birth)	Y (if not earlier)				
Prelacteal feeding	Child feeding tool		Y	Y (if not earlier)	Y	Y	Y	Y
Breastfeeding	Child feeding tool		Y	Y	Y	Y	Y	Y
Feeding other foods and drink	IYCF feeding tool		Y	Y	Y	Y	Y	Y
Feeding frequency	IYCF feeding tool		Y	Y	Y	Y	Y	Y
**Maternal dietary intake**								
Dietary diversity only	Dietary take tool			Y			Y	
**Household food security** (structured tool)	Food security assessment tool			Y		Y		Y
**Morbidity**								
Child morbidity (2-week recall)								
COPD for mothers	COPD assessment tool (CAT) for adult				Y	Y	Y	Y
Respiratory symptoms Children	ARI assessment				Y	Y	Y	Y
**HAP**								
HAP exposure (children)	Existing tool				Y	Y (12–16)		Y
**Gender**								
Gender questionnaire (women)	Adapted Pro-WEAI and CCA User Social Impact Survey				Y		Y	

##### Process evaluation

We will collect mixed-methods data to assess protocol adherence, LPG continued and exclusive and correct use, community engagement, awareness and knowledge of benefits and correct usage of LPG, and contextual factors for adherence and non-adherence of exclusive and continuous use of LPG. Data will be collected at regular time points using quantitative (regular project monitoring records/data) and qualitative methods (interviews and focus groups of a sub-sample of women and household members, and through direct observation). This data will assist with understanding adherence to the intervention (intensity of the intervention) and barriers and facilitators to clean cooking adoption, which will assist with identifying contextual factors influencing the trial outcomes, interpreting our trial findings, and also provide insight for replicating and scale-up.

### Plans to promote participant retention and complete follow-up {18b}

Our intervention is a high-value intervention and is itself a method to promote participant retention and complete follow-up. As this is an extension of the original trial we already know that participants are willing to continue with the intervention. Participants in the control arm receive small gifts (child blankets, toys and transport costs reimbursed) to promote retention and complete follow-up. Data will not be collected from those who discontinue with the intervention.

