#### Intervention description {11a}

The LPG fuel intervention for this extension will commence around birth when the previous cylinder is almost empty. Gas replenishment will continue free of cost until the infant is 24 months old. We have an existing LPG fuel distribution system in operation built into our electronic data collection system. We will continue with the same distribution process with this application. A national gas distribution company will supply the LPG with Bangladesh Standards and Testing Institution certification for cylinder quality. Based on the average duration of use of a cylinder by an average-sized household, we will require approximately 24 refills for each participant until the child is 24 months of age.

The intervention is distributed at the individual level but randomized at the cluster level to reduce community tensions and overall exposure and leverage community-level adoption of clean cooking. We will conduct outcome assessments at the individual level. Allocation concealment is impractical due to the cluster design and nature of the intervention. Participants and their households receive the intervention based on their cluster of residence (Fig. 2).

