**Fig. 2 Fig2:**
[figure not shown]
Flow diagram of Poriborton and Poriborton-Extension

Our field implementation team is trained in technical issues for gas stove installation, troubleshooting and maintenance, and cylinder replacement. They will continue to provide support to intervention households who require external assistance as necessary. These stoves will adhere to the Bangladesh Standards and Testing Institution requirements. We will replace the stoves in case of mechanical faults during the 2 years of use. Control women will continue with usual cooking practices (mostly traditional cooking) and will be followed up for outcome evaluation up to 24 months of child’s age. Participants from the control arm will be provided 200 Taka as time compensation during the six visits (3, 6, 12, 18, 24 months of child’s age).

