#### Outcomes {12}

The primary outcome for this trial will be the proportion of stunted children (height-for-age < − 2 Z) at 24 months in the intervention arm compared to the control arm.

Secondary outcomes include the following: (i) mean height-for-age *Z* scores, (ii) mean weight-for-length *Z* scores and prevalence of wasting (weight-for-length < − 2 Z) in children, (iii) mean absolute height-for-age differences, health outcomes: (iv) number of events and mean days with diarrhea, acute respiratory illness and fever, at 6, 12, 18, and 24 months of child’s age, (v) differences in Bayley Scales scores in cognitive, motor and language domains, and Wolke’s behavior ratings during Bayley test (vi) differences in household income/expenditure, (vii) cost of delivering the intervention and costs of upscaling, and (viii) cost-effectiveness of the intervention compared to usual cooking providing estimates of the incremental cost per stunted child prevented and incremental cost per disability-adjusted life years averted, (ix). Intermediate outcomes include PM2.5, 24-h averaged mean, and any differences in gender roles (self-efficacy, time use).

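### Toys are described as a retention gift for control families only, in a trial that records play materials at home and tests child development

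*Protocol article*

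**What the plan says.** The section on retention {18b} assigns incentives by arm. For the intervention arm: "Our intervention is a high-value intervention and is itself a method to promote participant retention and complete follow-up". For the other arm: "Participants in the control arm receive small gifts (child blankets, toys and transport costs reimbursed) to promote retention and complete follow-up". Neither sentence uses the word only, but the contrast makes control-only gifts the natural reading, and no section describes gifts for LPG families.

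The section on the family care indicator ties its questions to the Bayley visits. On their content, it says that they "will pick up information about child and caregiver interactions as well as availability of stimulation/play materials at home". Table 1 places both instruments at 12 and 24 months.

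Outcomes {12} lists, as secondary outcome (v), "differences in Bayley Scales scores in cognitive, motor and language domains", together with Wolke's behaviour ratings. Objectives {7} sets a target of 0.3 SD for child development at 24 months.

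Trial design {8} and the explanation of comparators {6b} define control as usual cooking practice, and Implementation {16c} states that control participants get no intervention.

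**The concern.** A retention gift should not act on anything the trial measures. Toys are play materials, and play materials at home are part of what the family care indicator records. If only control homes receive them, the trial itself creates an arm difference in those items. Home stimulation is also a plausible route to developmental scores, and the protocol evidently considers it relevant enough to measure beside Bayley.

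For development, the contrast delivered is then LPG against usual cooking plus toys, not LPG against usual cooking. If the toys have any developmental effect, it would be expected to favour controls and so hide part of a real LPG benefit, or suggest harm where there is none. The planned model (treatment as a fixed effect, cluster as a random effect) cannot separate a gift tied to arm from the treatment effect.

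**Working it through.** The article states no figure on this point, so there is none to reproduce. The main check is to set the sections side by side.

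1. Who gets toys: control participants (retention, {18b}). The LPG arm's incentive is the fuel.
2. What is measured: play materials at home (family care indicator) at 12 and 24 months, the same visits as Bayley and Wolke.
3. What control is meant to be: usual cooking with no intervention ({8}, {6b}, {16c}).
4. What the analysis can do: the model in Statistical methods {20a} estimates the arm difference, gifts included. Its secondary analyses adjust for imbalanced household characteristics. The family care indicator is not named there, but adjusting for its play-material items would mean adjusting for something the trial altered after randomization.

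Steps 1 and 2 establish that the play-material items can be affected directly. The further step to Bayley scores is an inference, and its size is not in the documents. The following is an illustration only.

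Inputs: 927 children per arm (Sample size {14}); 103 clusters per arm (Sequence generation {16a}), so 927/103 = 9 per cluster; two-sided 0.05; target 0.3 SD. Assumptions: the ICC of 0.02 given for stunting also applies to Bayley, and toys raise control scores by *b* SD.

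- Design effect = 1 + (9 − 1) × 0.02 = 1.16; effective n = 927/1.16 ≈ 799 per arm.
- Standard error of the difference = √(2/799) ≈ 0.050 SD.
- Power for a true 0.3 SD effect = Φ((0.3 − b)/0.050 − 1.96).
- Chance of a significant result against LPG when LPG has no effect = Φ(b/0.050 − 1.96).

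| Assumed b (SD) | Expected difference if true effect is 0.30 | Share of target hidden, b/0.3 | Power for 0.3 SD | Significant against LPG, no true effect |
|---|---|---|---|---|
| 0 | 0.30 | 0% | >99.9% | 2.5% |
| 0.05 | 0.25 | 17% | 99.9% | 16.8% |
| 0.10 | 0.20 | 33% | 97.9% | 51.6% |

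At ICC 0.04 the last column becomes 2.5%, 15.3% and 46.6%. The issue is therefore one of bias and not of power. The trial is precise enough on development for a small systematic shift to matter, if there is one.

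**The case against.** A reader might infer that the neurodevelopment comparison is biased against LPG, and that toys feed the Bayley scores directly. The documents do not support that. Bayley is a direct test, not a count of toys: "Appropriately qualified and trained staff will conduct the Bayley tests as per the manual". Any route from toys to scores runs through stimulation and is an outside inference. The gifts are called small, and nothing shows whether they come before the 12- or 24-month tests. Zero effect is possible, and the figures above follow entirely from the assumed b. This all stands, and it limits the claim to a possible bias of unknown size.

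A reader might also add the money and the blankets. The cash is described as payment for time ("Participants from the control arm will be provided 200 Taka as time compensation during the six visits") and has no stated link to development. A route from blankets to respiratory illness is speculation. Neither belongs in the point.

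It can be said that LPG families also receive something of value ("Gas replenishment will continue free of cost until the infant is 24 months old"), plus regular support visits, and that these could affect stimulation in the opposite direction. This stands as a caution: the net arm difference in the family care indicator could take either sign. It does not remove the problem. Free LPG and its household consequences belong to the treatment under test, whereas toys belong neither to LPG nor to usual cooking.

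The gifts also have a legitimate purpose. Control families need some reason to stay, and differential attrition would threaten every outcome, the primary included. That supports keeping a gift, but not choosing toys.

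Finally, a condensed article may leave out a gift schedule, and the full protocol might show tokens in both arms. The missing schedule is not the finding. The finding is the contrast the article does state.

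**Conclusion.** The point holds in a limited form. As written, toys for control families are an avoidable co-intervention that differs by arm. They can directly alter the play-material items of the family care indicator, and they may bias the Bayley/Wolke comparison against LPG by an amount the documents do not allow anyone to estimate.

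The family care indicator is not a listed outcome, so its contamination matters for use as a covariate or mediator and for interpretation. Stunting has no evident link to toys. The point should be acted on because child development is part of the stated aim and carries a 0.3 SD target, but it does not threaten the trial's main conclusion. It rests on reading the retention section as control-only, which its contrast supports but does not spell out.

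**What to change.** For the remaining visits, either replace toys with a gift of similar value unrelated to any measured outcome, or give the same items to both arms at the same visits. Both options keep an incentive for control families. State in the protocol what each arm receives and when.

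Log for each child which items were given and at what age, including those already handed out. Do not use the play-material items as an adjustment covariate, and do not read an arm difference in them as an LPG effect, without noting the gifts. Report the gifts alongside the Bayley and Wolke results.

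The cost is a swap of items, or a minor purchase for the LPG arm (about 1,030 children if the expected 2060 enrolled split evenly, 2060/2). Sample size does not change. Gifts already given cannot be undone. Trial status gives recruitment as complete in February 2022, so a change during follow-up would leave exposure to toys differing between children, which is a further reason for the log.
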